### Heart rate variability acquisition and analysis

As an exploratory outcome, resting-state electrocardiograms (ECGs) will be recorded before cardiopulmonary exercise testing at T0, T1, and T2. Participants will be placed in a supine position with eyes closed and breathing spontaneously, following a 10 min rest period, between 9:00 and 11:00 a.m., with no caffeine, tea, nicotine, or alcohol intake, and at least 2 h fasting. Using a Healink ECG device (Beijing Hailanxin Medical Technology Co., Ltd., China) with a standard V5 lead (positive electrode placed on the left anterior axillary line at the fifth intercostal space, negative electrode on the right midclavicular line at the first intercostal space), a 5 min ECG will be recorded (sampling rate 250 Hz). Artifacts in the RR interval series will be identified using a custom MATLAB program (RR < 300 ms or >1,500 ms, or a difference >50% from the adjacent RR interval), combined with visual inspection by human reviewers. Ectopic beats (premature atrial or ventricular contractions) will be identified by morphology, and their RR intervals will be replaced by interpolation of adjacent normal RR intervals. If the ectopic beat rate exceeds 5%, the corresponding data segment will be excluded from the primary analysis. Atrial fibrillation not identified at baseline and other rhythms unsuitable for conventional HRV analysis will be flagged as non-analyzable, excluded from the primary HRV analysis, and the proportion of excluded recordings will be reported separately (paced rhythms are already excluded by the exclusion criteria). Quality checks will be performed by two independent research assistants, with arbitration in case of disagreement. Time-domain (SDNN) and frequency-domain (HF, 0.15–0.40 Hz, autoregressive model) indices will be calculated using Kubios HRV Standard software (26). Frequency-domain indices will be natural-log transformed (ln-HF) before statistical analysis, while raw values will be reported as median (interquartile range). As an exploratory outcome, HRV will not be adjusted for multiple comparisons and will be used only for mechanistic interpretation.

HRV analysis will be performed by an independent researcher who is blinded to both group allocation (active vs. sham) and time point (T0, T1, T2). All ECG recordings will be anonymized by removing participant IDs, group information, and time point identifiers before batch analysis, so that the analyst will only see anonymous codes.

### Adverse event monitoring

Throughout the trial, participants will be instructed to proactively report any adverse events, including but not limited to: local skin irritation, erythema, dizziness, transient palpitations, nausea, headache, and tinnitus. All reported adverse events will be documented in detail in the case report form (including time of onset, duration, severity, management, and outcome). A serious adverse event is defined as an event that results in death, is life-threatening, requires hospitalization or prolongation of hospitalization, or causes significant disability. Severity will be graded using the CTCAE (Common Terminology Criteria for Adverse Events) (grades 1–5). Causality will be assessed by the investigator (related, possibly related, suspect, or unrelated). Serious adverse events will be reported to the ethics committee within 24 h. If a serious adverse event with a causal relationship to the intervention occurs, the participant will discontinue treatment but will continue to receive safety follow-up and outcome assessments. Their available data will still be included in the intention-to-treat analysis. At the same time, the participant will be immediately referred to the appropriate department for proper medical management. Safety monitoring will be conducted by the study coordinator, who will review adverse events monthly. Serious events will be jointly managed by the principal investigator and the responsible clinician. Given that the intervention is a low-risk, non-invasive transcutaneous electrical stimulation, an independent Data and Safety Monitoring Board will not be established.

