## Methods

### Study design

This study is a randomized, sham-controlled, parallel-group superiority trial. The study procedures and schedule are detailed in Table 1 (Study schedule and assessment timeline) and Figure 1 (Anticipated participant flow diagram).

**Table 1 T1:** Study schedule and assessment timeline.

Item	Assessment point T0 (Baseline)	Intervention phase (weeks 1–4)	Assessment point T1 (end of intervention)	Follow-up phase (weeks 5–8)	Assessment point T2 (follow-up assessment)
Time correspondence	Week 0	← 4 weeks →	End of Week 4	← 4 weeks →	End of Week 8
Enrollment and allocation					
Participant screening	●				
Informed consent	●				
Demographic data collection	●				
Medical history and medication record	●				
Randomization	●				
Intervention					
Experimental group (active taVNS)		●			
Control group (sham stimulation)		●			
Conventional rehabilitation training		●		●	
Primary outcome					
Cardiopulmonary exercise testing (VO_2_peak)	●		●		●
Secondary outcomes					
Inflammatory markers (IL-6, TNF-α)	●		●		●
NIHSS score	●		●		●
Modified Barthel index	●		●		●
Exploratory outcome					
Heart rate variability (SDNN, HF)^1^	●		●		●
Safety assessment					
Adverse event recording		●	●	●	●
Serious adverse event reporting		●			
Compliance monitoring					
Treatment session completion record		●	●		
Others					
Concomitant medication record	●	●	●	●	●
Unblinding request record		●	●	●	●

1 Heart rate variability (HRV), as an exploratory outcome, will be analyzed from 5 min resting-state electrocardiograms recorded before cardiopulmonary exercise testing at T0, T1, and T2. It will not be subjected to multiplicity correction and will be used only for explanatory analyses. T0 = baseline assessment point (pre-intervention assessment and randomization); T1 = post-intervention assessment point (end of week 4); T2 = follow-up assessment point (end of week 8). The intervention phase spans weeks 1–4, and the follow-up phase spans weeks 5–8. The symbol “●” indicates that the procedure or assessment is performed at the corresponding time point.

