### Intervention

A transcutaneous auricular vagus nerve stimulation device manufactured by Jiangxi Jingyi Medical Technology Co., Ltd., China, will be used. Stimulation electrodes will be placed over the vagus nerve distribution hotspot in the left auricular concha (23, 24). The stimulation parameters are: biphasic square wave, frequency 25 Hz, pulse width 200 µs, single session duration 30 min (25). The stimulation intensity will be individually adjusted based on each participant's sensory threshold. The sensory threshold is defined as the minimum current intensity at which the participant first clearly perceives a tingling sensation on the skin surface (starting from 0.1 mA and increasing slowly). The stimulation intensity in the active taVNS group will be set at a level that is just at or slightly above the sensory threshold (i.e., an intensity that the participant can clearly perceive without pain), typically between 0.5 and 1.5 mA, to ensure a clear, comfortable, and non-painful stimulation sensation. Treatment will be administered once daily, five days per week, for a total of 4 weeks. The sham stimulation group will use the same device, electrode placement, and operational procedures as the active stimulation group. Consistent with previous studies (25), the stimulation current will be set to 0 mA throughout the entire 30 min session. The indicator lights and buzzer sounds of the device will be synchronized with those of the active stimulation group throughout the treatment period.

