Both groups will receive standardized conventional rehabilitation training delivered by the same rehabilitation team during the intervention period (weeks 1–4), consisting of 4 weeks, 5 days per week. The training includes: physical therapy (once daily, 40 min): positioning and transfer training (5 min), affected lower limb weight-bearing training (10 min), sit-to-stand transfer training (10 min), balance training (10 min), and walking training (5 min); and occupational therapy (once daily, 30 min): activities of daily living training (e.g., dressing, eating, grooming) and upper limb functional training. All training will be supervised one-on-one by uniformly trained therapists. Training intensity will be assessed every 5 days according to the patient's Brunnstrom stage and modified Barthel Index score, following an individualized progression principle. Training performance will be recorded in a standardized training log and reviewed weekly by the study coordinator. Adjustments to the duration of individual modules based on the patient's functional characteristics are permitted, provided the total duration remains unchanged; however, adding or removing training modules is not allowed. During the follow-up period (weeks 5–8), participants will continue to receive the same conventional rehabilitation training as in the intervention period (with unchanged content, frequency, and supervision), but will no longer receive taVNS or sham stimulation. Training performance will continue to be recorded and reviewed.

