### Data collection

Demographic characteristics (age, sex, education level), stroke-related medical history (disease duration, stroke type, lesion location), comorbidities, and current medication lists will be collected for all participants and recorded in the case report form. During the 2-week period before baseline and throughout the trial, medications affecting heart rate, heart rate variability, exercise tolerance, or inflammation (including beta-blockers, calcium-channel blockers, antiarrhythmic agents, anticholinergic medications, antidepressants, sedatives, corticosteroids, and other anti-inflammatory agents) will be maintained at stable doses unless medically indicated otherwise. Any medication adjustments will be documented in detail (drug name, dose, reason for adjustment, and date), and will be included as covariates in the final statistical analysis. The actual duration, intensity, completion rate, and content of rehabilitation training will be recorded separately for each group. Physical activity outside the study and additional rehabilitation interventions will be documented through weekly follow-up interviews. In the final report, the number and reasons for all screening failures will be recorded, particularly the proportion of patients excluded due to inability to complete CPET.

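### Adverse events are gathered from participants' own reports and routinely reviewed only monthly in a four-week treatment; a weekly review and one prompted checklist for both arms would be a cheap improvement

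*Protocol article*

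**What the plan says.** **Capture.** Under Adverse event monitoring, "participants will be instructed to proactively report any adverse events", with seven example symptoms named. What then reaches the record is what was reported: "All reported adverse events will be documented in detail in the case report form". Table 1 (Study design) marks "Adverse event recording" for the intervention phase, T1, the follow-up phase and T2. No section describes a standard question or checklist.

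**Review.** "Safety monitoring will be conducted by the study coordinator, who will review adverse events monthly". The same section says that there will be no independent monitoring board, and gives the low risk of the intervention as the reason. Serious events go to the ethics committee within 24 hours. Events are graded by CTCAE and the investigator judges causality, with no timing given.

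**Exposure.** "Treatment will be administered once daily, five days per week, for a total of 4 weeks" (Intervention). Active current is set at a level the participant can clearly feel; sham is 0 mA for the whole session.

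**Contacts that already run weekly.** Training performance is "recorded in a standardized training log and reviewed weekly by the study coordinator" (Intervention). Under Data collection, outside activity and "additional rehabilitation interventions will be documented through weekly follow-up interviews". Under Allocation and blinding, a research assistant who does not give treatment asks each participant for a group guess once a week in weeks 1 to 4.

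**Analysis.** Statistical methods compares adverse event incidence between arms with Fisher's exact test.

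**The concern.** There are two separate weaknesses.

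The first is timing. The routine review comes round about once per treatment course. A non-serious event in the first session can be followed by as many as 19 further sessions before the coordinator's scheduled look. The same protocol has a coordinator look at training logs every week.

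The second is comparability. Events enter mainly when a participant chooses to mention them. One arm feels a current and the other feels nothing, and the Limitations section accepts that participants may guess their group from sensation. A person who feels the device may be readier to mention dizziness, palpitations or tinnitus than one who does not. Fisher's test sees only the reported counts, so it cannot separate a difference in incidence from a difference in reporting.

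At stake is the safety comparison, which is a planned result of the trial. The primary efficacy analysis is not touched.

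**Working it through.** The plan gives no figure of its own on this point, so there is nothing to reproduce first.

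**1. Length of the course** (Intervention)
- Sessions: 5 per week × 4 weeks = 20.
- Monday start: three full weeks plus Monday to Friday = 3 × 7 + 5 = 26 days from first to last session.
- Any other weekday start: 28 days.

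**2. Chance that no routine review falls within the course**

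Monthly means an interval of 28 to 31 days. The article does not say whether it runs by calendar or by participant.

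For reviews at a fixed interval and a random start, the share with no review between first and last session is 1 − (span − 1)/interval, or zero if that is negative.

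| Interval (days) | Span 26 days | Span 28 days |
|---|---|---|
| 7 | 0% | 0% |
| 14 | 0% | 0% |
| 28 | 1 − 25/28 = 10.7% | 1 − 27/28 = 3.6% |
| 30 | 1 − 25/30 = 16.7% | 1 − 27/30 = 10.0% |
| 31 | 1 − 25/31 = 19.4% | 1 − 27/31 = 12.9% |

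As a check, all weekday start dates in the planned recruitment period (July 2026 to June 2027) were enumerated, with a review on a fixed day of the month (days 1 to 28 in turn). The share was 17.9% for Monday starts and 12.5% for starts on any weekday.

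If review instead happens one month after each participant's own start, it falls 28 to 31 days in. A 26- to 28-day course is then over, or at its last session, for essentially everyone.

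**3. What unequal reporting could do** (assumed rates; none are in the document)

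Take a true incidence of 15% in both arms, 80 per arm, and 90% of active-arm events reported. Observed active rate: 0.15 × 0.90 = 13.5%.

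| Sham events reported | Observed sham rate | False difference | Fisher rejects at 0.05 |
|---|---|---|---|
| 90% | 0.15 × 0.90 = 13.5% | 0 points | 3% |
| 75% | 0.15 × 0.75 = 11.25% | 2.25 points | 5% |
| 60% | 0.15 × 0.60 = 9.0% | 4.5 points | 10% |

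The last row is about 11 against 7 participants (80 × 0.135 = 10.8; 80 × 0.09 = 7.2), for which Fisher's p is 0.45. On these assumptions the harm is a distorted estimate more than a false significant result.

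**4. What equal under-reporting could do** (assumed rates, 80 per arm, exact power of the two-sided Fisher test)

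| True incidence | All captured | 75% captured | 50% captured |
|---|---|---|---|
| 20% vs 5% | 79% | 62% | 37% |
| 30% vs 10% | 87% | 71% | 48% |

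Missed events therefore also lower the chance of seeing a real difference.

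**5. Passages that do not agree**
- Recording window: Adverse event monitoring and Table 1 cover the whole trial through T2; Safety assessment speaks of events in the intervention period.
- Recorder: Safety assessment gives recording to the research coordinator; Allocation and blinding describes an independent research coordinator who knows every allocation. The article does not say whether these are the same person.

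**The case against.** The monthly review is best read as an added trial-level check. Each reported event is entered with onset, severity, management and outcome, graded, and judged for causality. None of this is tied to the monthly cycle. Participants are seen five days a week, and serious events leave within 24 hours. This stands: a reader might infer that the monthly review is the only oversight of non-serious events, and the document does not support that. It does not say when the investigator's assessment takes place either.

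A reader might also infer that participants in general finish treatment unreviewed. On a calendar schedule it is a minority. With enrolment spread over twelve months, a pattern across participants would still come up monthly.

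Calling the reports unprompted would also go too far. Participants are given named symptoms, and recording is scheduled at T1 and T2. Whether staff ask a set question there may be in the full protocol or case report form, which are not shown. So the absence of a checklist is not in itself an error. The point is that the stated method can be improved at little cost.

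Finally, the reporting rates have no source, and a checklist cannot remove a bias that comes from an unfelt sham. Both are correct. They limit how large the problem can be said to be, and what the fix can promise.

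**Conclusion.** The point holds as an inexpensive improvement to the stated method. The monthly interval is about as long as the 26- to 28-day course. About 13% to 18% of participants could complete it without a routine review of non-serious events if reviews follow the calendar. The closed form spans 4% to 19% over intervals of 28 to 31 days, and the share is nearly all if review is timed from each participant's start. Review every 7 or 14 days brings it to zero.

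The threat to the between-arm comparison is real in mechanism: felt current in one arm, none in the other, and reports started by the participant. Its size is unknown, and its direction rests on an assumption about who speaks up. The 4.5-point example is an illustration, not an estimate. The document does not show that the safety comparison will be misleading, or that serious events would be missed.

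**What to change.** 1. In Adverse event monitoring, change the coordinator's review from monthly to weekly, alongside the weekly training-log review. After an event, at most 5 further sessions would then pass before a routine look.
2. Ask the same prompted checklist in both arms, using the protocol's own listed events. In weeks 1 to 4 the research assistant who asks the blinding question can do this. In weeks 5 to 8 it has to be the weekly interview under Data collection, because the assistant's contact ends at week 4. Repeat it at T1 and T2.
3. State that whoever asks does not know the allocation. This needs confirming for the assistant, and for the interviewer, whom the article does not identify.
4. Report prompted and volunteered events separately by arm.
5. Reconcile the recording window between Adverse event monitoring with Table 1 and Safety assessment. State whether the coordinator who records events is the one aware of allocation.

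**Cost.** Protocol and case report form wording before enrolment opens, and a few minutes at contacts that already take place. More minor events will be recorded in both arms. Prompting narrows reporting differences but does not remove those that come from the unfelt sham.

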### Data collection

Demographic characteristics (age, sex, education level), stroke-related medical history (disease duration, stroke type, lesion location), comorbidities, and current medication lists will be collected for all participants and recorded in the case report form. During the 2-week period before baseline and throughout the trial, medications affecting heart rate, heart rate variability, exercise tolerance, or inflammation (including beta-blockers, calcium-channel blockers, antiarrhythmic agents, anticholinergic medications, antidepressants, sedatives, corticosteroids, and other anti-inflammatory agents) will be maintained at stable doses unless medically indicated otherwise. Any medication adjustments will be documented in detail (drug name, dose, reason for adjustment, and date), and will be included as covariates in the final statistical analysis. The actual duration, intensity, completion rate, and content of rehabilitation training will be recorded separately for each group. Physical activity outside the study and additional rehabilitation interventions will be documented through weekly follow-up interviews. In the final report, the number and reasons for all screening failures will be recorded, particularly the proportion of patients excluded due to inability to complete CPET.

### Outcome measures

#### Primary outcome measure

The primary outcome of this study is VO_2_peak, with the body-weight-normalized value (mL/kg/min) as the unique primary endpoint. It will be assessed by cardiopulmonary exercise testing at three time points: baseline (T0, pre-intervention), post-intervention (T1, after completion of the 4-week treatment), and follow-up (T2, 4 weeks after the end of the intervention). The absolute value (L/min) will be reported as a supportive measure. The primary efficacy time point is T1 (end of intervention), with T2 (end of follow-up) as a secondary time point for assessing persistence of the effect.

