### Statistical methods

Statistical analyses will be performed using SPSS 26.0 and R 4.1.0, following the intention-to-treat principle. All tests will be two-sided, with a significance level of *α* = 0.05 unless otherwise specified for multiple comparisons. Statisticians will remain blinded to group allocation until data lock. All randomized participants will be retained in the intention-to-treat analysis. The per-protocol analysis will report the proportion and characteristics of participants who do not meet the effort criteria. Additional stratified analyses will be considered: (1) all randomized participants; (2) those meeting adequate-effort criteria; (3) those terminating due to cardiopulmonary limitation; and (4) those terminating due to neurological or motor limitation, to assess the robustness of the results. For the primary outcome, VO_2_peak will be analyzed using a linear mixed-effects model, with group, time, and their interaction as fixed effects and participant as a random effect (random intercept) to account for within-subject correlations; a random slope may be added if model fitting requires. Age, sex, baseline VO_2_peak, stroke type, disease duration, baseline National Institutes of Health Stroke Scale score, and recruitment source (hospital or community) will be included as prespecified covariates. In the model, the time factor (T0, T1, T2) is used to estimate longitudinal trends, while baseline VO_2_peak is included solely as a covariate to adjust for baseline differences; the two serve different functions and do not constitute redundant adjustment. The covariance structure will be selected from unstructured, compound symmetry, or first-order autoregressive models based on the Akaike information criterion or Bayesian information criterion. The primary treatment effect will be assessed based on the baseline-adjusted between-group difference in VO_2_peak at T1, and the effect estimate, 95% confidence interval, and corresponding *p*-value will be reported. For secondary outcomes, all four measures (interleukin-6, tumor necrosis factor-alpha, National Institutes of Health Stroke Scale, and modified Barthel Index) will be analyzed longitudinally using the same linear mixed-effects model as for the primary outcome. For variables with substantial deviation from normal distribution or violations of parametric assumptions, generalized linear mixed models or nonparametric methods will be used as supplements. To control for multiple comparisons, a Bonferroni correction will be applied for the four secondary outcomes, with the significance threshold set at *α* = 0.05/4 = 0.0125. The exploratory outcome (heart rate variability) will not be adjusted for multiple comparisons and will be used only for exploratory interpretation. For missing data, the primary analysis will use the linear mixed-effects model under the missing-at-random assumption, utilizing all available observed values. To assess robustness, multiple imputation by chained equations and per-protocol analysis will be conducted as sensitivity analyses. In addition, the originally prespecified repeated-measures analysis of variance will be performed as a complementary analysis for comparison with the primary results; if the sphericity assumption is violated, the Greenhouse-Geisser correction will be applied, and *post-hoc* comparisons will be performed using the Bonferroni method. The incidence of adverse events will be compared using Fisher's exact test. If the sample size permits, prespecified exploratory subgroup analyses will be conducted for stroke type (ischemic vs. hemorrhagic) and recruitment source (hospital vs. community), using interaction tests to assess potential effect modification, with results interpreted only as exploratory. Due to sample size constraints (80 participants per group), stratification was performed only for age and disease duration. Other heterogeneity factors, including stroke type, baseline NIHSS score, and baseline VO_2_peak, have been incorporated as prespecified covariates into the linear mixed-effects model for adjustment.

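### VO2peak at T2 is named as the test of persistence but has no place in the multiplicity scheme: it defaults to two-sided 0.05 and is not conditional on T1

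*Protocol article*

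**What the plan says.** Under Primary outcome measure, the Protocol article makes weight-normalized VO2peak the sole primary endpoint and T1 the primary time point, "with T2 (end of follow-up) as a secondary time point for assessing persistence of the effect". Statistical methods follows this: "The primary treatment effect will be assessed based on the baseline-adjusted between-group difference in VO_2_peak at T1".

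The error-control rules are all in Statistical methods:

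- The default: "All tests will be two-sided, with a significance level of *α* = 0.05 unless otherwise specified for multiple comparisons".
- The correction: "a Bonferroni correction will be applied for the four secondary outcomes, with the significance threshold set at *α* = 0.05/4 = 0.0125". The members are listed as "all four measures (interleukin-6, tumor necrosis factor-alpha, National Institutes of Health Stroke Scale, and modified Barthel Index".
- The exemption: "The exploratory outcome (heart rate variability) will not be adjusted for multiple comparisons".
- A Bonferroni rule for post-hoc comparisons, attached to the complementary repeated-measures ANOVA and not to the primary mixed model.

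None of these names VO2peak at T2.

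**The concern.** Primary outcome measure creates a secondary efficacy comparison on the primary variable, and the scheme in Statistical methods does not place it anywhere. Only the default of 0.05 is left for it. The four other secondary outcomes are held to 0.0125. Where the plan wants a result to be exploratory it says so (heart rate variability, ventilatory threshold, subgroups), and it does not say so here.

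The stated purpose of T2 also implies an order that is never written down. An effect can persist only if it was present at the end of treatment. As the rules stand, a trial with a non-significant T1 result could still report a significant VO2peak difference at T2, from the same model and on the trial's main variable.

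**Working it through.** **The plan's own figure.** 0.05/4 = 0.0125, which reproduces exactly. It covers four outcomes, and T2 VO2peak is not one of them.

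**Inputs.**
- Two-sided alpha of 0.05 for T1 (the primary test) and for T2 (by the default), from Statistical methods.
- Correlation among repeated measures 0.50, within a typical range of 0.3 to 0.7, from Sample size calculation.
- Assumptions added here: the two test statistics are bivariate normal, and the repeated measures have compound symmetry.

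**Correlation between the T1 and T2 tests.** After adjustment for baseline, the correlation of T1 and T2 given T0 is (ρ − ρ²)/(1 − ρ²). At ρ = 0.50 this is (0.50 − 0.25)/(1 − 0.25) = 0.33. At ρ = 0.3 it is 0.23, and at ρ = 0.7 it is 0.41. The unadjusted value of 0.5 is carried alongside.

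**Chance under the null that T1 or T2 is significant.** This is P(|Z1| > 1.96 or |Z2| > 1.96). If the tests were independent it would be 1 − 0.95² = 0.0975. T2-only is this value minus the 0.05 that belongs to T1. By symmetry, half of T2-only favours taVNS.

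| Correlation of tests | T1 or T2 | T2 only, two-sided | T2 only, favouring taVNS |
|---|---|---|---|
| 0 | 0.0975 | 0.0475 | 0.024 |
| 0.33 | 0.0946 | 0.0446 | 0.022 |
| 0.5 | 0.0907 | 0.0407 | 0.020 |
| 0.7 | 0.0835 | 0.0335 | 0.017 |
| 0.9 | 0.0704 | 0.0204 | 0.010 |

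Over the plan's own range of ρ (0.3 to 0.7, baseline-adjusted), the T1-or-T2 figure moves only from 0.096 to 0.093.

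**Effect of possible remedies.**
- Testing T2 only after a significant T1: a false positive on either requires a false positive at T1, so the chance is 0.05 under the null at both visits. T1 alpha, power and sample size do not change.
- Adding T2 VO2peak to the secondary family: the threshold becomes 0.05/5 = 0.01, and the T1-or-T2 chance is 0.057 at correlation 0.5.
- Splitting alpha 0.025/0.025 between T1 and T2: at 64 per group and d = 0.5 (the planned f = 0.25 under the plan's f = d/2), a two-sample t-test at T1 falls from power 0.801 to 0.712.

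**The case against.** The strongest reply is that the trial has one primary test. The endpoint, the time point and the contrast are each fixed to T1, and Ethics and dissemination repeats T1 as the registered primary time point. This stands. A reader might infer from the 0.09 to 0.095 figure that the primary type I error is nearly doubled. The document does not support that, because the figure describes a T1-or-T2 claim that the plan never defines as its success criterion.

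It can also be said that the T2 threshold is inferred. An estimate, interval and p-value are promised explicitly only for T1, and no sentence specifies a T2 test. That is true, but the default is worded to cover all tests and no other threshold is offered.

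A third reply is that the stated purpose of T2 already limits its use, so a T2-only efficacy claim would fall outside it. This is a fair reading, and it means the two sections do not contradict each other. What is missing is a rule that enforces the reading.

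Finally, leaving a later visit as supportive is common, and a separate analysis plan may set the order. But the article does not defer multiplicity: it states a default, a family, a threshold and an exemption, and this comparison has no stated place among them.

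**Conclusion.** The point holds as a narrow gap in the multiplicity scheme. VO2peak at T2 is a named secondary comparison, outside the corrected family, not labelled exploratory, and at two-sided 0.05 by default with no condition on T1. The T1 test keeps its 0.05 error. If there is no effect at either visit, a false T2-only benefit for taVNS appears in about 2% of trials (4.1 to 4.5% counting both directions). This rests on the plan's correlation of 0.50, compound symmetry and approximate normality.

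Two further inferences should not be drawn:

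- **T2-only significance when there is a real effect.** With 64 per group and the same true effect at both visits, it occurs in about 15 to 20% of trials at d = 0.2 to 0.3, and in 7.4% at d = 0.5. These are real effects missed at T1, not false claims, and the plan does not use the smaller effect sizes.
- **A combined secondary error of 0.083.** This is the figure for T2 plus the four corrected outcomes at correlation 0.5 and one visit each. It cannot be set against an intended 0.05, because the plan states no such target for those five tests together.

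**What to change.** State in both Primary outcome measure and Statistical methods that VO2peak is tested first at T1 at two-sided 0.05, and at T2 at two-sided 0.05 only if T1 is significant. If T1 is not significant, the T2 estimate and 95% confidence interval are reported descriptively, with no claim of persistence or efficacy. The separate 0.0125 rule for the four other outcomes can stay as it is.

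The cost is one or two sentences. No participants, data or T1 power are given up, and T2 keeps its full 0.05 whenever T1 succeeds. The only downside is that a T2-only result can no longer be claimed as confirmatory. Recruitment is planned from July 2026 and the article says no trial data have been examined, so the rule should be fixed before enrolment, while it cannot be suspected of being data-driven.
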